| Comparator product(s)                         | Placebo                                                                                                                                                                                                                                                                                                                                                                                                                                                                                                                                                                                                                                                                                                                                                                                                                                                                                                                                                             |
| Route(s) of administration                    | Oral                                                                                                                                                                                                                                                                                                                                                                                                                                                                                                                                                                                                                                                                                                                                                                                                                                                                                                                                                                |
| Maximum duration of treatment of a Patient    | 112 days                                                                                                                                                                                                                                                                                                                                                                                                                                                                                                                                                                                                                                                                                                                                                                                                                                                                                                                                                            |
| Procedures: Screening & enrolment             | 
 
Participants will attend the unit for a screening visit within 45 days prior to administration of the first dose of trial medication. Written informed consent must be obtained prior to performance of any protocol specific procedures. The following procedures will be performed: 
 
Medical history including smoking history
 
Current medication history prior to the screening visit.
 
Demography (date of birth, age, gender and race)
 
Physical examination including height, weight, BMI, seated blood pressure and heart rate
 
Spirometry post bronchodilator
 
Standard, supine 12-lead ECG (triplicate)
 
Following an overnight fast, blood (approximately 55ml) and urine will be collected for clinical chemistry, haematology, HIV, Hepatitis B surface antigen, Hepatitis C antibody, urinalysis.
 
 
 
 |
| Trial period:                                 | 
Participants will be entered into the trial for a period of up to 171 Days (approximately 6 Months).
 
Participants will be asked to attend for up to 8 visits. These will consist of 2 scanning visits at V2 & V8. V3, V4, V5, V6, V7 and V9 participants will have a number of tests performed as listed below, they will also receive study medication during this period.
                                                                                                                                                                                                                                                                                                                                                                                                                                                                                                                                                                       |
| End of Trial                                  | 
The end of trial definition will be 3 months after last participant last visit.
 
 
Physical examination including seated blood pressure (BP) and heart rate (HR).
 
Blood (approximately 55mL) and urine will be collected for clinical chemistry, haematology, urinalysis.
 
Bloods for biomarkers.
 
Adverse event and concomitant medication check.
 
                                                                                                                                                                                                                                                                                                                                                                                                                                                                                                                                   |
| Procedures for safety monitoring during trial | Clinical safety data is a secondary endpoint of this trial. The safety and tolerability of protocol-specified treatments will be assessed by physical exam findings, 12-lead ECGs recordings, vital                                                                                                                                                                                                                                                                                                                                                                                                                                                                                                                                                                                                                                                                                                                                                                 |

|                                                       |                                                                                                                                                                                                                                                                                                                                                                                                                                                                                                         |
|-------------------------------------------------------|---------------------------------------------------------------------------------------------------------------------------------------------------------------------------------------------------------------------------------------------------------------------------------------------------------------------------------------------------------------------------------------------------------------------------------------------------------------------------------------------------------|
|                                                       | 
signs (blood pressure and heart rate) measurements, clinical laboratory tests (including LFT), clinical monitoring /observation and spontaneous and elicited adverse event reporting. Methodology for safety assessments will be on file at the clinical research unit.
 
The Trial Steering Committee (TSC) will provide overall supervision for the trial, to ensure that it is conducted in accordance with the protocol and GCP and to provide advice through its independent chairman.
 |
| Criteria for withdrawal of patients on safety grounds | 
Participants will be withdrawn from the trial if they experience a SUSAR. At the discretion of the PI/CI, participants will be withdrawn if they experience a SAE, which would affect their ability to participate in the trial.
                                                                                                                                                                                                                                                                 |

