| EudraCT number for proposed trial                | 2011-004936-75                                                                                                                                                                                                                                                                                                                                                                |
| Medical condition or disease under investigation | COPD (Chronic Obstructive Pulmonary Disease)                                                                                                                                                                                                                                                                                                                                  |
| Purpose of clinical trial                        | To test the hypothesis that stratifying a COPD population on plasma fibrinogen improves the ability to observe a response to an anti-inflammatory treatment in the vasculature and lungs. In this trial, Losmapimod will be used as a tool to test the hypothesis of stratification.                                                                                          |
| Primary objectives                               | To determine the effect of Losmapimod in COPD patients on vascular structure and function as assessed by 
 
1. Vascular inflammation
 
2. Endothelial function
 
3. Arterial structure and plaque characteristics
 
                                                                                                |
| Secondary objective (s)                          | To determine the effects of Losmapimod on 
 
1. Inflammation in lung tissue
 
2. Inflammation in fat
 
3. Arterial stiffness
 
4. Blood biomarkers of inflammation
 
5. Indices of lung function and physical performance
 
6. Body composition and fat
 
7. Safety and tolerability
 
 |

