## **7 Introduction**

### **7.1 Background**

Chronic obstructive pulmonary disease (COPD) is the fourth leading cause of death globally and the only major cause that is predicted to increase in the coming decades. Although COPD is initially a pulmonary disease (traditionally caused by cigarette smoke, but increasingly by biomass fuel exposure), it is a complex condition in which outcome is in large part, driven by cardiovascular and systemic components. Consistent with this, although current bronchodilator-based interventions have demonstrated reduced exacerbation rates, this has only addressed part of the burden of disease. In particular, drugs currently used neither reduce the rate of disease progression nor mortality, creating a space in the market for products which could do so. This unmet need and the implied requirement for new strategies for the development of non-bronchodilator therapies for COPD have been recognized by Regulatory agencies as evident from recent guidance documents from the EMA and FDA.

The role of inflammation in COPD is well-recognised. A range of inflammatory markers and cytokines are raised in COPD patients, and relate to the severity of lung function and important clinical outcomes such as admission, cardiovascular events and death. Elevated fibrinogen (indicating a systemic 'inflammatory' phenotype) is a robust, stable biomarker that occurs in at least 25% of patients with COPD, and is associated with increased morbidity and mortality. Inflammation modulates large artery stiffness, an independent determinant of cardiovascular mortality, and anti-inflammatory therapies reduce arterial stiffness, providing a novel mechanism by which inflammation may drive cardiovascular risk.

Losmapimod is a ATP binding site inhibitor of p38 $\alpha$  MAPK and is currently being developed by GSK for a variety of inflammatory conditions, including COPD.

The ERICA programme is a series of studies designed to clarify the role of inflammation in extra-pulmonary disease manifestations in COPD. This trial will assess the role of stratifying patients on the basis of systemic inflammatory biomarkers against parameters of vascular, pulmonary and skeletal muscle phenotypes. This may enable the development of better biomarkers to design smaller, more efficient phase I-III clinical trials of novel drugs that target inflammatory COPD subsets thereby reducing attrition of new medicines.

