Rupture of atherosclerotic plaques can lead to myocardial infarctions and cause sudden cardiac deaths. Such vulnerable plaques have typical histopathological features that include the presence of a thin fibrous cap, extensive lipid core and an associated inflammatory infiltrate. Macrophages, key inflammatory cells, abound in these plaques and imaging of these macrophages is an appealing approach to detect plaque inflammation that may lead to clinical complications. Recently, FDG-PET/CT has demonstrated success in detecting plaque inflammation within the aorta, carotid and vertebral arteries and has been validated histologically, as correlating with macrophage content and/or activity, both in human and animal models of disease. COPD patients have previously been demonstrated to have increased FDG uptake suggesting increased background vascular inflammation in this group.

The main goals of this experimental trial are to test the hypothesis that stratifying a COPD population on plasma fibrinogen improves the ability to observe response to an anti-inflammatory treatment known to reduce fibrinogen as well as reduce inflammatory activity in the extra-pulmonary and pulmonary spaces in these patients. Therefore, Losmapimod will be used as a tool to test the hypothesis that it improves vascular health in inflamed COPD patients.

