## **10 Selection and withdrawal of participants**

### **10.1 Inclusion Criteria**

A patient will be eligible for inclusion in this trial only if all of the following criteria apply:

1. Male or female patients between 50 and 85 years of age inclusive at screening, with a body weight  $\geq 45$  kg and BMI  $\leq 35$  kg/m^2.
2. Patients with a clinical diagnosis of COPD with GOLD Stages 1, 2, 3 or 4, or GOLD-U. Gold U are patients with a clinical history consistent with COPD and a reduced FEV1 but a preserved (i.e.  $>0.7$ ) FEV1/VC ratio in the absence of an alternative diagnosis. For the purpose of EVOLUTION, establishing an absence of an alternative diagnosis will normally include as a minimum physical examination of the thoracic cage, a normal chest radiograph and the demonstration of a maximal sniff nasal inspiratory pressure  $>50$  cm H2O
3. Patient has FEV1/FVC  $< 0.7$  post-bronchodilator.
4. Patient is a smoker or an ex-smoker with a smoking history of at least 10 pack years (1 pack year = 20 cigarettes smoked per day for 1 year or equivalent).
5. Baseline fibrinogen value of  $>2.8$  g/L (Klauss method)
6. ALT  $< 2 \times$ ULN at screening; alkaline phosphatase and bilirubin  $\leq 1.5 \times$ ULN at screening (isolated bilirubin  $>1.5 \times$ ULN is acceptable if bilirubin is fractionated and direct bilirubin  $<35\%$ ).
7. Patients must have a QTc  $<450$  msec on screening (V1) ECG (using average value of triplicate ECGs). For patients with complete Right bundle branch block, the QTc must be  $<480$  msec on Screening V1 ECG. Patients with other ECG findings will be excluded if warranted at the discretion of the CI/PI. QTc readings will be QTcF.
8. (For the optional MRI sub-study (n/a if patient does not consent to MRI)): Patients who fulfil local imaging centre requirements will be enrolled.

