### 11.2 Clinical Data

#### 11.2.1 Efficacy

After completion of phase I trials in healthy volunteers, Losmapimod 7.5 mg BD was studied in a 12 week randomized clinical trial in COPD patients. Heat shock protein, a downstream effector of p38 MAP kinase was significantly reduced compared with placebo after 4 and 12 weeks of therapy in the group that received losmapimod (ratio of effect of Losmapimod/placebo 0.56, 95% CI 0.43 to 0.73,  $p < 0.001$  at 4 weeks and ratio of effect of Losmapimod/placebo 0.61 95% CI 0.46 to 0.82,  $p < 0.001$  at 12 weeks). Losmapimod significantly reduced plasma fibrinogen by 11% ( $-0.4 \text{ g/L}$ , placebo adjusted mean at 12 weeks  $3.6 \text{ g/L}$ , Losmapimod adjusted mean at 12 weeks  $3.2 \text{ g/L}$ ; ratio of effect of Losmapimod/placebo 0.89, 95% CI 0.83 to 0.96;  $p = 0.002$ ). There was a trend in ratio

of effect for Losmapimod/placebo of 0.81 for IL-6 (95% CI 0.63 to 1.03; p=0.09), 0.83 for IL-8 (95% CI 0.66 to 1.04; p=0.10) and 0.76 for CRP (95% CI 0.55 to 1.06; p=0.10). The administration of Losmapimod resulted in a non-significant increase in post-bronchodilator forced vital capacity (92mL; 95% CI: -5 to 190mL; p=0.06) and non-significant reductions in both residual volume (124mL; 95% CI: -9 to 257mL; p=0.07) and thoracic gas volume (113mL, 95% CI: -20 to 246mL; p=0.09) when compared to placebo (Table 2). There was no effect on inspiratory capacity.

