### **11.9 Treatment Assignment**

Participants will be randomised to the Losmapimod or Placebo regimen in a 1:1 ratio. The randomisation will be stratified by treatment centre. A delegated member of the trial team will log into the website <https://prod.tenalea.net/cctu/DM/default.aspx> using a secure password. They will enter the following information

- Subject Number
- Subject Initials
- Subject DoB
- Confirmation of eligibility
- Inc/Exclusion criteria confirmation

The system will provide a box number which will be used by the site pharmacy to provide the treatment allocated in a double-blinded manner.

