Formal ANCOVA analysis will be performed on the change from baseline, with fixed effects for the treatment and adjustment for baseline value and treatment centre. Estimates of the treatment effect, (Losmapimod – Placebo) will be provided with 95% confidence intervals and p-values. All estimated regression parameters will be reported in a similar fashion. Comparisons of proportions will be handled using a similar approach based on logistic regression to estimate odd ratios.

As an exploratory trial the focus will be estimation and interpretation of treatment effects and not on formal hypothesis tests. As such no adjustment for the extensive multiple testing will be done.

Secondary endpoints will have similar summary measures reported broken down by time-point and treatment group. Endpoints that are repeatedly observed in the intermediate visits during treatment will be summarised graphically. Regression analysis may be performed.

A detailed statistical analysis plan will be finalised prior to data base lock, although it is anticipated that this will be the first stage in reporting and subsequent post-hoc analyses will be performed and documented as being post-hoc.

Figure 1 illustrates some of these derived variables.

[figure not shown]

Figure 1: Stylised diagram of an artery to demonstrate the various PET indices that are derived from the regions of interest (ROI) placed on the vessel. A circular ROI is drawn to encompass the vessel wall on each contiguous axial segment. Each axial segment then provides two numbers: a mean and a maximal value for the FDG uptake within that segment, expressed as the TBR. The MeanMean TBR is the averaged Mean TBR values from each artery. The MeanMax TBR is the averaged Max TBR values from each artery. The most diseased segment (MDS) is centred on the darkest red segment, defined as having the highest maximal TBR value in the entire artery. When averaged with the segments immediately above and below it, these three segments yield the MDS. Example values and their derivations are provided in the lowest row

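### The stated purpose, testing whether stratifying on fibrinogen helps reveal a response, cannot be answered because every participant must be above 2.8 g/L

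*Protocol*

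**What the plan says.** The Trial Synopsis states the purpose as "To test the hypothesis that stratifying a COPD population on plasma fibrinogen improves the ability to observe a response to an anti-inflammatory treatment" and adds: "In this trial, Losmapimod will be used as a tool to test the hypothesis of stratification". Section 8 says the same: "The main goals of this experimental trial are to test the hypothesis that stratifying a COPD population on plasma fibrinogen improves the ability" to see a response. Section 7.1 has a matching sentence on assessing the role of stratifying by systemic inflammatory biomarkers.

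The design elements that bear on this are:

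- **Entry (section 10.1, criterion 5).** "Baseline fibrinogen value of" more than 2.8 g/L. All inclusion criteria must be met, so this binds every participant. Section 8 accordingly calls the sample enriched.
- **Randomisation (section 11.9).** "The randomisation will be stratified by treatment centre". Fibrinogen is not a stratum.
- **Model (section 16.1).** "Formal ANCOVA analysis will be performed on the change from baseline, with fixed effects for the treatment and adjustment for baseline value and treatment centre". No fibrinogen term is named.
- **Objectives (section 9.5).** These ask for the effect of losmapimod on vascular and other measures. None refers to stratification.
- **A narrower hypothesis (section 8).** After the stratification goal, the text also sets out to test whether losmapimod benefits the vessels of COPD patients who are inflamed.

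**The concern.** A claim that stratifying improves detection compares two situations: looking for a response in patients selected on fibrinogen, and looking for it without that selection. The trial creates only the first.

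If losmapimod shows an effect, it may work equally well at any fibrinogen level, and selection then added nothing. If it shows none, the selection idea may be sound and the drug inactive on these endpoints. Neither result separates these explanations. The risk is that the report presents the stratification hypothesis as tested, and that a later programme adopts or drops fibrinogen selection on that basis.

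**Working it through.** **1. The quantity that the purpose needs.** Let p be the share of COPD patients above 2.8 g/L, D_H the losmapimod effect above the cut and D_L the effect at or below it. The effect in unselected patients is

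D_U = p·D_H + (1 − p)·D_L,

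so the gain from selection is

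D_H − D_U = (1 − p)·(D_H − D_L).

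The trial estimates D_H. It has 0 participants at or below the cut, so D_L, and with it the gain, cannot be estimated at any sample size. The ability to observe a response also depends on variability, and the SD without selection is not observed either. Section 16.4 takes its SD from a trial in established atherosclerosis and uses it only for precision.

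**2. The plan's own precision figure.** Section 16.4 assumes an SD of 0.3 and 30 per arm, and states a 90% chance of a 95% half-width of 0.17 or less. The half-width is q·s·√(2/n), with s² distributed as 0.3²·χ²(58)/58.

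| Multiplier q | Half-width at s = 0.3 | 90th percentile | P(half-width ≤ 0.17) |
|---|---|---|---|
| normal, 1.96 | 0.152 | 0.169 | 0.908 |
| t, 58 df | 0.155 | 0.173 | 0.861 |

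The figure reproduces with the normal multiplier, and to two decimals with t. It is the precision of D_H, not of the gain from selection.

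**3. What the contrast would have required.** Assume two equal fibrinogen strata, 1:1 allocation within each and SD 0.3 in every cell; the protocol gives no such design. The half-width for D_H − D_L is t·0.3·√(4/m), with m per cell.

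| Per cell (m) | Total | Half-width for D_H − D_L |
|---|---|---|
| 15 | 60 | 0.310 |
| 30 | 120 | 0.217 |

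A 90% chance of 0.17 or less would need about 55 per cell, 4 × 55 = 220 in total. At the planned 60, the interval would be twice as wide as that for the overall effect (0.310 against 0.155).

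**4. What the enrolled sample could offer.** A treatment-by-continuous-fibrinogen slope within the 60 participants has an approximate 95% half-width of

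2 · 2 · 0.3 / (√60 · SD_fib) = 0.155 / SD_fib.

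The fibrinogen SD among enrolled patients is not in the protocol. For assumed values of 0.5, 0.6 and 0.8 g/L the half-width is 0.31, 0.26 and 0.19 TBR per g/L. This describes a gradient above 2.8 g/L. It is not D_H − D_U.

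**The case against.** **The objectives are sound.** The objectives, endpoints, model and precision statement all concern the effect of losmapimod and fit the enrolled sample. The trial is exploratory and disclaims formal hypothesis testing. This stands, and it limits the severity: the fault lies in the stated purpose, not in the treatment estimate. It does not rescue a purpose on which the data carry no information.

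**The analysis plan may deal with it.** A plan could add a fibrinogen term, but it cannot supply patients at or below 2.8 g/L.

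Three stronger readings are tempting, and the documents do not support them.

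- *Fibrinogen is measured but never related to the treatment effect.* Section 12.7 allows optional work on pre-dose profiles that might predict response, and sections 16.1 and 16.3 defer detail to plans not seen here. The most that can be said is that the model in section 16.1 names no fibrinogen term.
- *The 2.8 g/L cut hardly selects.* A reader might set the 3.6 g/L in section 11.2.1 against the statement in section 7.1 that raised fibrinogen "occurs in at least 25% of patients with COPD". But 3.6 g/L is a "placebo adjusted mean at 12 weeks", not a baseline distribution, and neither its SD nor that trial's fibrinogen eligibility is given. The 25% is a lower bound for an elevation with no stated threshold. The share of patients above the cut cannot be derived from these.
- *A null result would be uninformative.* A narrow interval around zero would limit the size of effect in patients above the cut. It would leave open only the comparison with unselected patients.

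**Conclusion.** The point holds and is of moderate severity. The purpose in the synopsis and section 8 is comparative, and one side of the comparison has 0 participants by design. This follows from the entry criterion alone and needs no numerical assumption. The figures for a two-stratum design and for the slope do rest on assumptions: SD 0.3 throughout, equal strata for the former, and a fibrinogen SD of 0.5 to 0.8 g/L for the latter. They show scale only. The planned estimate of the losmapimod effect above 2.8 g/L remains valid, as does the narrower hypothesis in section 8 about inflamed patients.

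**What to change.** **Needed.** In the synopsis purpose, the main-goals sentence of section 8 and the matching sentence of section 7.1, state the purpose as estimating the effect of losmapimod in COPD patients with fibrinogen above 2.8 g/L. This agrees with section 9.5.1 and with the narrower hypothesis in section 8. Add that the benefit of selection over no selection cannot be concluded from this trial. The cost is wording.

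**Optional.** Name one PET variable, since section 16.1 lists many without a lead, and add continuous baseline fibrinogen and its interaction with treatment to that ANCOVA as an exploratory model. Report the slope with its 95% interval and describe it only as a gradient above 2.8 g/L. Fibrinogen is already measured at V1 and V3, so no new data are needed, but the plan must say which measurement is the baseline. The downside is the wide interval shown in the working.
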